***SELF-ASSESSMENTS QUESTIONNAIRES***			
***MOCA***		X	X
***HHIE-S***		X	X
***AQoL***		X	X
***IOI-HA***			X

Baseline (t0):

Signature of the Patient giving Informed Consent..

First assessment (Pre):

otoscopy and cleaning of the external auditory canal (if required).unaided pure tone audiometry (right and left ear).unaided speech audiometry in quiet (right and left ear).Italian version of Oldenburg Satztest (OLSA test) [19].Self-assessment questionnaires:Montreal Cognitive Assessment (MoCA) [20].Hearing Handicap Inventory in the Elderly Screening test (HHIE-S) [21].Assessment of Quality of Life *(*AQoL) [22].Abbreviated Profile of Hearing *A*id Benefit (APHAB) [23]..

Second assessment (Post):

otoscopy and cleaning of the external auditory canal (if required).test of the HA functioning.unaided pure tone audiometry (right and left ear).aided speech audiometry in quiet (in free field).Italian version of OLSA test.Self-assessment questionnaires:

MoCA.HHIE-SAQoL.International Outcome Inventory for Hearing Aids (IOI-HA) [24].APHAB in aided condition.

To complete all the measures takes approximately one hour: 30 minutes for performing the standard self-report questionnaires and 30 minutes for the other tests.

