#### Selection Criteria

Inclusion:

Age > = 65 years.First use of unilateral or bilateral HA.HA partially or totally funded by the Italian National Health System.Willingness to participate in.Willingness to comply with all study procedures.Fluency in italian language used to assess clinical performance.Able to decide on study participation personally.Able to independently sign their consent..

Exclusion:

Unilateral hearing loss.Previous use of HA.Significantly/severely dependent or fragile.Unable to provide consent personally.Unable to complete questionnaires for self-assessment independently.Significant comorbidities preventing study participation.Subjects with unrealistic expectations on benefits, risks and limitations concerning the procedure and prosthetic device..

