#### Montreal Cognitive Assessment (MoCA)

Montreal Cognitive Assessment (MoCA) is a cognitive screening instrument used to detect mild cognitive impairment, a high-risk condition for dementia forms [20, 36–38].

It is composed of 12 subtasks assessing different cognitive skills, including short-term and delayed verbal memory, executive function, and attention. The total MoCA score ranges from 0 (worst performance) to 30 (best performance). Mild cognitive dysfunction is suspected when the final score is less than 26.

Different strategies will be integrate by clinicians in order to avoid a misdiagnosis or overdiagnosis of cognitive impairment. Personnel will be trainedto administrationof this tool in patients with hearing loss. In particular, they will assess the correct use of hearing aids; they will ensure that the test environments meet standards for ambient noise levels and they can use alternative presentation modality of the items with auditorycontents (with multimodal presentation: both auditory and visual presentation) [39].Santangelo et al. produced the normative data for the Italian population [20].

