### Statistical considerations:

An intrasubject endpoint comparison is to be used for primary and secondary study objectives. The pairwise comparisons are of interest: previous use of HA (Pre)-to-12 months HA use (Post).

Investigation will apply multivariate exploratory factor analysis to reduce the number of variables and identify possible latent factors, followed by Spearman correlation to analyze the relationships between the variables and the factors.Finally regression analysis will apply to investigate how factors and variables relate to each other and how they predict outcomes.

Data will be analyzed by nonparametric tests for categorical variables and by t-test for continuous variables.

Questionnaires analysis will be performed by using a nonparametric test.

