During this study two-time point, tonal unaided audiometry was used to check any auditory threshold modification and worsening of the audiometric clinical situation over time. Speech audiometry in unaided conditions in the first assessment and in aided conditions in the second assessment were used because it describes the sample and allows it to be compared to the existing literature.

The second objective of this study is based on the evaluation of possible improvements in the overall health-related quality of life in the sample.

To verify this aim, self-report questionnaires were chosen, which are essentially non-verbal and consequently remove challenges directly associated with utilizing new HA. The percentage of subjects who improve the questionnaire score using HA (second assessment) compared to the first evaluation in unaided conditions is to be evaluated.

Improvement in quality of life can be evaluated by using different questionnaires. The AQoL questionnaire is used in this study because of its robust psychometric characteristics and wide diffusion in the health-related quality of life literature. In a review by Mihalopoulos et al., (thatanalyzesinstruments for depression outcome measurements) report that AQoL-8D “had the highest correlation with the disease-specific measurements and the best goodness-of-fit transformation properties” [28].

The HHIE has been included in the study in order to better understand the effects of hearing impairment on emotional and social adjustment in everyday life. It is one of the most widely applied questionnaires with respect to auditory participation and has been reported with both HA and cochlear implant recipients [41]. A significant reduction of the questionnaire score in Post vs. Pre-evaluation is expected in this study, which suggests quality of life improvement.

The MoCA questionnaire was chosen to screen the cognitive abilities of subjects. The use of this questionnaire will exclude deficits in these abilities. Using this test in Pre and Post evaluation will verify that cognitive abilities do not affect other questionnaires and HA results. The use of the MoCA questionnaire in the Pre and Post evaluation will exclude a reduction of the cognitive abilities over time. A reduction of these abilities can be a sign of the deterioration of the general state of health that may affect the execution of the other questionnaires used. The same score is expected in Pre and Post evaluation of the same subject.

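### An unchanged MoCA score from Pre to Post cannot show that cognition left the hearing-aid and questionnaire results unaffected

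*Protocol article*

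**What the plan says.** The protocol article's Discussion gives the MoCA two roles that bear on how the results will be read. The first: "The use of this questionnaire will exclude deficits in these abilities". The second: "Using this test in Pre and Post evaluation will verify that cognitive abilities do not affect other questionnaires and HA results". It adds that the repeat test will rule out a loss of cognitive ability during the year, because such a loss could disturb the other questionnaires. The one expectation it sets is: "The same score is expected in Pre and Post evaluation of the same subject".

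Elsewhere in the article:

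- The MoCA section gives a level: "Mild cognitive dysfunction is suspected when the final score is less than 26". No action, stratum or analysis is attached to it.
- Table 1 puts the eligibility screen, consent and allocation at t0, and MoCA at Pre and Post.
- Selection Criteria contains no cognitive score. The nearest exclusions are functional or general: "Unable to complete questionnaires for self-assessment independently" and "Significant comorbidities preventing study participation", together with severe dependence or frailty and inability to consent.
- Statistical considerations names the Pre-to-Post comparison, an exploratory factor analysis, Spearman correlations and a regression among factors and variables that are not listed.

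**The concern.** Whether cognition changed during the year and whether cognition influences the outcomes are different questions. The first concerns a within-subject difference. The second concerns the relation between a subject's level and that subject's gain. The Discussion answers the second with a check that addresses only the first. Low but stable cognition passes that check, yet it may go with a smaller OLSA gain or less reliable questionnaire answers.

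What is at stake is a conclusion about who benefits. The article intends its results for health policymakers. A statement that deficits were ruled out and that cognition played no part would be read as covering mildly impaired users, although the stated check cannot support it.

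**Working it through.** The article gives no figure on this point to reproduce: no MoCA distribution, no SD for OLSA change, and no alpha or power behind the sample of about 100. The main argument is therefore logical, and the arithmetic only illustrates it.

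**1. The stated check applied to one subject.** Take a score of 20 at Pre and 20 at Post. The difference is 0, so the expectation of an equal score is met. The level is below 26, so mild dysfunction is suspected at both visits. No selection criterion uses the score, and MoCA comes after the eligibility screen. The subject is enrolled and analysed, the check is passed, and a deficit has not been ruled out.

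**2. Illustration of a passed check alongside a real influence.** Assumed values, none from the article:

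- n = 100; true MoCA mean 24, SD 3; measurement SD 1.5 at each visit; no true change.
- OLSA gain (Pre minus Post SNR) = 2 + 0.3 × (true MoCA − 24) dB, with residual SD 2.

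Results over 4,000 simulated studies:

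- The Wilcoxon Pre-Post MoCA test rejects in 5.4% of runs. This is its nominal rate, as it must be when nothing changes.
- About 72% of subjects score below 26. By formula: SD of observed MoCA = √(3² + 1.5²) = 3.35, and Φ((26 − 24)/3.35) = 0.72.
- The mean Spearman correlation between Pre MoCA and gain is 0.34.
- Reading the article's 1.5 dB threshold as an improvement, the share exceeding it is 23 percentage points higher at MoCA 26 or above than below 26.

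The mean gain is about 2 dB in this population whether or not MoCA is examined. The influence of cognition changes who gains; it does not bias the average.

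**3. Would a direct test be able to verify no effect?** By Fisher's z, two-sided 0.05, n = 100:

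- Smallest correlation with 80% power: tanh((1.960 + 0.842)/√97) = tanh(0.284) = 0.28.
- Power at r is Φ(atanh(r) × √97 − 1.960): 17% at r = 0.1, 51% at r = 0.2, 86% at r = 0.3.

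Even the right analysis would often miss a modest influence, so a non-significant result must not be reported as no effect.

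**4. What an interval would give.** Under the assumptions of step 2:

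- SD of gain = √(2² + 0.3² × 3²) = 2.19 dB.
- Covariance of Pre MoCA and gain = 0.3 × 9 = 2.7, so the slope on observed Pre MoCA is 2.7/11.25 = 0.24 dB per point. This is below 0.3 because of measurement error.
- Residual SD = √(4.81 − 2.7²/11.25) = 2.04, and SE = 2.04/(3.35 × √100) = 0.061.
- The 95% half-width is about 1.96 × 0.061 = 0.12 dB per point, which shows the reader which influences remain possible.

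**The case against.** The strongest reply is that this is loose wording in a Discussion section.

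- The planned Spearman correlations and regression can take MoCA in. It is a collected variable, and cognitive status is part of the secondary aim. Which covariates enter is commonly left to an analysis plan that is not shown. This stands: the absence of a named MoCA analysis is not the fault. The fault is that the Discussion rests its claim on repeating the test and expecting equal scores, not on those analyses. No later detail can make a change score answer a question about level.
- The Discussion's worry about decline during the year is legitimate, and a Pre-Post MoCA comparison suits it. This also stands.
- Each subject is their own control, and mildly impaired older adults belong in a consecutive cohort. Stable low cognition may modify the gain but does not bias the mean change in those enrolled. This stands and limits the consequence.
- The functional exclusions will remove some severe impairment. That is true, but they set no limit near 26.
- The illustration assumes its effect, and the 5% figure is only a null test rejecting at its own level. Agreed. It shows that the check does not respond to level, not how large the influence is in this cohort.

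A reader might infer from the word *exclude* that subjects with low scores are to be removed after enrolment. The text does not support this. The same verb is used shortly afterwards for a decline over time, where it can only mean to rule out, and no section describes removing anyone.

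**Conclusion.** The claim that Pre and Post MoCA will rule out deficits and show that cognition does not affect the other results does not follow from the stated check. Equal scores speak to decline over the year. They leave open the influence of baseline level, and a subject below 26 at both visits satisfies them.

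The reach of the point is limited. It would be going too far to infer that the primary Pre-Post OLSA comparison is invalid, or that the planned methods could not address the question. The comparison stands, and the generic correlation and regression could include MoCA. Nor does the article prescribe a reporting statement that would hold whatever the data show: low scores and falling scores would both be visible.

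The logical point needs no assumption. The figures (5.4% rejection, 23 percentage points, 17% to 86% power for r from 0.1 to 0.3) are illustrations on assumed values and are not estimates for this study.

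**What to change.** 1. Limit the Pre-Post MoCA comparison in the Discussion to what it can do: detect decline over the year.
2. Replace the sentence on verifying no influence with an analysis placed within the regression already planned in Statistical considerations. Regress OLSA change, and the HHIE-S, AQoL-8D and APHAB changes, on Pre MoCA as a continuous variable. Report each slope with its 95% CI, and state that a non-significant slope is not evidence of no effect.
3. Replace the sentence on excluding deficits with a report of the number of subjects below 26 at Pre, keeping all enrolled subjects in the main analysis.

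Whether a cognitive limit belongs among the entry criteria is for the investigators, and nothing here requires one. The cost is some rewording and one regression per outcome, since MoCA is already collected at Pre. The small downside is that the hoped-for statement that cognition does not affect the results may not hold.

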**Methods:**

The monocentric, prospective, repeated measurements, single-subject, clinical observational study is to recruit 100 older adults, first-time HA recipients (≥ 65 years).The evaluation protocol is designed to analyze changes in specific measurement tools a year after the first HA usage in comparison with the evaluation before HA fitting.

Evaluations will consist of multiparametric details collected through self-report questionnaires completed by the recipients and a series of commonly used audiometric measures and geriatric assessment tools. The primary indicator of changes in speech perception in noise to be used is the Italian version of Oldenburg Satz (OLSA) test whereas the indicator of changes in overall quality of life will be the Assessment of Quality of Life (AQoL) and Hearing Handicap Inventory for the Elderly (HHIE) questionnaires. The Montreal Cognitive Assessment (MoCA) will help in screening the cognitive state of the subjects.

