## Methods and design

### Study aims

The primary aim of this study is to identify whether or not there is any significant improvement in speech recognition in noise in older adults patients ( > = 65 years) who are using HA for the first time. This improvement is to be verified by using a Signal to Noise Ratio (SNR) reduction which will be evaluated using the OLSA test.The secondary aim is to process the correlations between the use of the HA and quality of life and cognitive status in older adults. Any improvement or deterioration can be seen in higher or lower scores in auto-assessment questionnaires.

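### Repeating the MoCA at Pre and Post cannot exclude cognitive deficits or decline, and cannot verify that cognition leaves the other results unaffected

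*Protocol article*

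**What the plan says.** All references are to the protocol article.

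- **Abstract, Methods.** The MoCA is a screening tool: "The Montreal Cognitive Assessment (MoCA) will help in screening the cognitive state of the subjects".
- **Study aims.** Cognition belongs to the secondary aim, which is to "process the correlations between the use of the HA and quality of life and cognitive status in older adults".
- **Timing schedule, Table 1.** Eligibility screening, consent and allocation are at t0. The MoCA is scheduled at Pre and Post.
- **Selection Criteria.** No criterion names the MoCA or cognitive impairment. The nearest are indirect: ability to decide and consent personally, absence of comorbidities that prevent participation, and the exclusion "Unable to complete questionnaires for self-assessment independently".
- **Montreal Cognitive Assessment (MoCA).** A threshold describes the instrument and is not used as an eligibility or analysis rule: "Mild cognitive dysfunction is suspected when the final score is less than 26".
- **Discussion.** On deficits: "The use of this questionnaire will exclude deficits in these abilities". On influence: "Using this test in Pre and Post evaluation will verify that cognitive abilities do not affect other questionnaires and HA results". On the expected result: "The same score is expected in Pre and Post evaluation of the same subject". The same paragraph says that the repeated test will rule out a loss of cognitive ability over time.
- **Statistical considerations.** Exploratory factor analysis, Spearman correlation and regression are planned in general terms, and questionnaires are to be analysed nonparametrically. The MoCA is not named as a predictor, covariate or stratifier.

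**The concern.** The Discussion draws three conclusions from measuring the MoCA twice: deficits are absent, decline is absent, and cognition has no bearing on the other results. The first needs an entry rule, and none is listed. The second needs an estimate precise enough to rule out a decline that matters. The third needs an analysis of association, because constancy of a variable over time and its influence on other variables are separate properties.

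At stake is how the secondary results are read. The Discussion says that the outcomes are meant to inform healthcare policymakers. A report following this paragraph could present the OLSA and quality-of-life changes as free of cognitive influence, and the cohort as cognitively stable, when the stated check supports neither statement.

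**Working it through.** The documents give no power, margin, SD or expected change for the MoCA, so there is no figure of the plan to reproduce. Parts 2 and 3 use assumed inputs and serve only as illustration.

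**1. Are deficits excluded?** Eligibility is settled at t0 and the MoCA is first done at Pre. The listed criteria contain no MoCA score. A subject who scores below 26 at Pre therefore meets the criteria as written, provided that he or she can consent and complete the questionnaires unaided. Those requirements filter out severe impairment, but not the mild dysfunction that the threshold of 26 is meant to flag.

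**2. Does a stable score show that cognition has no influence?** A simulation checked this.
- From the document: n = 100 subjects.
- Assumed: MoCA mean 24, SD 3, test-retest correlation 0.8, no true change from Pre to Post, two-sided 5% level, 3,000 replicates. Hearing-aid benefit correlates with underlying cognition at rho = 0, 0.3 or 0.5.

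| rho | Pre-Post MoCA test significant (Wilcoxon signed-rank) | Baseline MoCA against benefit significant (Spearman) |
|---|---|---|
| 0 | 5.8% | 4.9% |
| 0.3 | 5.2% | 73% |
| 0.5 | 5.5% | 99% |

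The Pre-Post comparison stays near 5% whether cognition is unrelated or strongly related to benefit, so it carries no information on the question. The direct association test responds.

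The expectation of an identical score in each subject is also unrealistic. Under the same assumptions about 78% of subjects would score differently at the two visits from retest noise alone. That percentage depends on the assumed SD and retest correlation.

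**3. Does failure to detect a change exclude decline?**
- Assumed: true mean decline 0.5 points, SD of change 2, 2.5 or 3, two-sided 5% paired t-test, 100 complete pairs.
- Noncentrality = 0.5 / (SD / √100). The critical value is t(0.975; 99 df) = 1.984. The probability of missing the decline is 1 minus the power from the noncentral t distribution.

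| SD of change | Noncentrality | Probability of missing the decline | 95% CI half-width, 1.984 × SD / 10 |
|---|---|---|---|
| 2 | 2.50 | 0.30 | 0.40 |
| 2.5 | 2.00 | 0.49 | 0.50 |
| 3 | 1.67 | 0.62 | 0.60 |

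With 80 complete pairs, also an assumption, the probabilities are 0.40, 0.58 and 0.69.

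Free of any assumed SD, the mean change detectable with 80% power is (1.96 + 0.84) / √100 = 0.28 SD of the differences, and about 0.32 with 90% power (normal approximation).

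The t-test is a stand-in, since the article plans a nonparametric test for questionnaires. The figures are approximate for that reason.

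**The case against.** The strongest reply is that these are Discussion sentences explaining why an instrument was chosen, and that the means to answer the question are already planned. Statistical considerations includes Spearman correlation and regression relating variables to one another and to outcomes, and the MoCA is among the variables collected. Which covariates enter a model is commonly left to a statistical analysis plan. The Discussion also disclaims causal investigation. Most of this stands: the absence of a named covariate is not itself a fault. It does not rescue the paragraph, because the verification is said to come from using the test at Pre and Post, not from those analyses.

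Partial safeguards also count. Subjects must be able to consent and to complete questionnaires unaided, and the MoCA section provides for trained staff, controlled ambient noise and multimodal presentation. These improve the measurement and filter severe impairment. They do not exclude mild deficits.

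A reader might infer stronger criticisms that the documents do not support:
- **That subjects who decline will be dropped, biasing the OLSA and quality-of-life changes.** No section removes anyone on a MoCA result, and the natural sense of the wording is ruling out a decline.
- **That a non-significant test will be read as no decline, or that a stable group mean is the criterion.** The article states no decision rule and speaks of the same subject, not of a mean. The flaw in inferring no influence is the same for individual stability.
- **That cognition cannot be both part of the secondary aim and expected to stay constant.** A variable can be an outcome and an explanatory variable, and expecting no change is compatible with studying correlations.
- **That subjects below 26 will certainly be enrolled.** This follows from the criteria as listed. The article describes the MoCA as screening, so an unlisted rule in the full protocol is possible.

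**Conclusion.** The point holds in limited form. As written, the claim to exclude deficits has no counterpart in the selection criteria, and the inference from an unchanged MoCA score to no cognitive influence is invalid. That conclusion is one of logic and does not depend on the assumed values.

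A claim that decline is excluded would likewise be unsupported if it rested on failure to detect a change. The size of that problem, a miss probability of about 30% to 62% with 100 pairs, rests on an assumed 0.5-point decline, an assumed SD of change of 2 to 3, and a t-test in place of the planned nonparametric test. Nothing in the documents says whether 0.5 points matters.

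The consequence is confined to how the secondary and supporting results are interpreted. The primary OLSA comparison is unaffected.

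**What to change.** 1. **Reconcile the Discussion with Selection Criteria.** State whether any MoCA result bears on eligibility. If one does, list it. If none does, withdraw the statement that deficits are excluded. That choice is the sponsor's.
2. **Replace the sentence on verification with a direct analysis.** Within the regressions already planned, use Pre MoCA as a predictor of OLSA change and AQoL-8D change, with MoCA change as a predictor in a supporting analysis. Report coefficients with 95% confidence intervals. A non-significant coefficient should not be read as no influence: by the Fisher z approximation, Φ(atanh(r) × √97 − 1.96), power with 100 subjects is about 51% for a correlation of 0.2 and 86% for 0.3.
3. **Report the Pre-Post MoCA change with a 95% confidence interval.** Do not claim that decline is excluded because a test is non-significant. Drop the expectation of an identical score in each subject.

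The cost is a few sentences of protocol text and some additional model output, using data already collected. The claims of no cognitive influence and no decline become harder to make, and the interval may be too wide to support either.

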## Background

Hearing loss is one of the most common disabilities in the world. Prevalence of this disease increases with age and its estimated prevalence is 40–50 % in people older than 75 years [1].

The term presbyacusis refers to decreased hearing sensitivity in older adults subjects. Nevertheless, this term has a broader meaning including all types of hearing loss that occur in the older adults. Presbyacusis also involves genetic age-related cumulative effects and potential secondary injuries to the auditory system (noise-induced hearing loss, ototoxicity, etc.).

Presbyacusis is the main cause of stable hearing loss and the most common disablingdisease in the older adults. [2].

Presbycusis is characterized by a bilateral symmetrical neurosensorial hearing loss that initially involves high frequencies and secondarily medium and low frequencies. Auditory threshold modifications are related to variations in detection, localization and speech discrimination especially in noisy environments [3, 4]. These variations deteriorate sociality, sensitivity, cognition, and quality of life of the subject [5–7].

However, cognitive abilities can benefit from the hearing-impaired subject using a hearing aid (HA). It is clear that hearing loss and cognitive abilities are linked and influence each other [8, 9].

Periodic monitoring of the hearing threshold is essential in early identification of communication disability or handicap, and the initiation of early treatment.

Since presbycusis is a multifactorial disease, the decline of the auditory threshold can be reduced by limited noise exposure, medical treatment in case of systemic or ear diseases or, in most cases, by using a HA [10–12].

Various studies have shown that HA improve quality of life (QoL) and cognitive functions in patients with presbycusis [8, 13–15]. Compared to patients with untreated hearing loss, patients with HA show improvements in social and emotional scores, communication and cognition skills, and do not suffer so much from depression [16].

In most studies, HA benefit is investigated using traditional clinical audiometric tests or self-assessed outcomes [17]. Only a few studies use multiparametric experimental protocols that explore both audiometric and cognitive skills improvement in older hearing-impaired subjects with HA [7].

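### MoCA change is both an outcome of the secondary aim and a stability check expected to show nothing, and the check cannot support the claim made for it

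*Protocol article*

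**What the plan says.** **As an outcome.** Study aims: "The secondary aim is to process the correlations between the use of the HA and quality of life and cognitive status in older adults". The next sentence says how the answer is to be read: "Any improvement or deterioration can be seen in higher or lower scores in auto-assessment questionnaires". MoCA is not named there. The link comes from two other places. The visit list under Timing schedule places MoCA among the self-assessment questionnaires at both Pre and Post, and Table 2 (Materials) marks it as the only tool for the cognition domain, although under clinician report. The Background supplies a reason to expect movement: "Various studies have shown that HA improve quality of life (QoL) and cognitive functions in patients with presbycusis".

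**As a screen and validity check.** The abstract gives MoCA the task of screening cognitive state. The Discussion goes further and claims a verifying role for it: "Using this test in Pre and Post evaluation will verify that cognitive abilities do not affect other questionnaires and HA results". It also states what it expects to find: "The same score is expected in Pre and Post evaluation of the same subject". A separate sentence there gives MoCA a screening purpose: "The use of this questionnaire will exclude deficits in these abilities". The Discussion reads a decline as a possible sign of worsening general health that could disturb completion of the other questionnaires. It also restates the second objective as health-related quality of life, without cognition.

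**Analysis.** Statistical considerations applies one within-subject Pre-Post comparison to the primary and secondary objectives. It adds factor analysis, Spearman correlation and regression, and specifies a nonparametric test for questionnaires. It does not say which role of MoCA governs.

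**The concern.** An expected null result is not in itself a fault, since a variable can be a secondary outcome and still be expected to stay stable. The difficulty is that stability is also used as evidence that the other results are sound. A finding of interest under the aim then becomes a departure from what the Discussion relies on, and a null finding under the aim becomes a passed check. The article gives no rule for choosing, so the meaning of the MoCA result could be settled after the data are seen.

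The second problem does not depend on the first. Even if MoCA were only a check, constancy over one year is the wrong evidence for the claim that cognition does not influence the questionnaires and hearing-aid results. At stake are the interpretation of the cognition part of the secondary aim and a reassurance about OLSA, AQoL and HHIE-S that the data could not give.

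**Working it through.** No sample size, error rate or effect size enters this point, and the article gives no figure to reproduce. The check is a comparison of the sections.

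**Step 1: is MoCA tied to the secondary aim?** The aim includes cognitive status. Table 2 has one mark in the cognition row, under MoCA. MoCA is given at Pre and Post. No other listed instrument can serve that part of the aim, so the link holds by inference, not by name.

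**Step 2: read each possible result under both roles.**

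| Pre-Post MoCA | Study aims (outcome) | Discussion (check) |
|---|---|---|
| Rise | Improvement in cognition | Departure from the expected equal score |
| No change | No improvement or deterioration | Check passed |
| Fall | Deterioration in an outcome | Sign of general decline that may compromise the other questionnaires |

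The first two rows give different readings of the same data. In the third row both readings are unfavourable, but one is a result and the other a reason to doubt different results.

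**Step 3: test the verification claim.** The MoCA section gives a range of 0 to 30 and suspects mild cognitive dysfunction below 26. Take two hypothetical subjects with constant scores:

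- Subject A scores 25 at both visits, one point below the threshold: change = 25 − 25 = 0.
- Subject B scores 30 at both visits, the top of the scale: change = 30 − 30 = 0.

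Both meet the expectation of an equal score. Their cognitive levels differ, and both contribute to OLSA, AQoL and HHIE-S. If level of cognition affects how a subject answers or how much the aid helps, a check on change cannot see it. Zero change is compatible with any effect of level.

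**Step 4: does enrolment close the gap?** The selection criteria contain no MoCA threshold, and Table 1 schedules MoCA at Pre and Post, not at the eligibility screen. Subjects such as A can therefore be in the cohort unless another criterion keeps them out.

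**The case against.** The best counter-argument is that most of the text points to screening. The abstract names AQoL and HHIE as the quality-of-life indicators and MoCA as a screen, the Discussion's second objective omits cognition, and Study aims names neither MoCA nor a direction. The Background sentence reports other studies and is not this study's hypothesis. All of that stands. It shows that Study aims may be the section out of line, and that making MoCA an outcome is not the only valid repair. It does not remove the inconsistency, and it does not rescue the verification claim, which fails under a pure screening role too.

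A reader might infer more than the article supports:

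- *That the cognition aim has no interpretable answer.* The Pre-Post MoCA difference and its correlations can still be computed and reported under Statistical considerations, and the Discussion disclaims causal investigation. What is missing is a single pre-stated meaning.
- *That the aim cannot fail because every result suits one role.* A fall is unwelcome under both, and it is a real possibility in people aged 65 or over followed for a year.
- *That subjects whose MoCA changed will be dropped or adjusted for.* Nothing says so. The statement about excluding deficits can mean ruling them out, as in the later sentence about decline over time, and the absence of a MoCA entry criterion fits that reading.
- *That the expectation must fail because few stable subjects score identically twice.* This takes the phrase as exact equality for each person, where no systematic change is a natural reading. It also needs a standard deviation of the difference that the article does not give.

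**Conclusion.** The point holds in two parts. First, MoCA change has two incompatible pre-stated uses: an outcome by way of Study aims and Table 2, and a stability check in the Discussion, with the abstract supporting a screening role. Second, the claim that Pre and Post MoCA will show cognition does not affect the other results is invalid as written, because constancy says nothing about the effect of level.

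The reach is limited. The primary OLSA comparison is not altered, and the MoCA data remain usable. No bias can be quantified and none is asserted. The first part assumes that MoCA is the instrument meant for the cognition part of the aim, which Table 2 supports. The second part needs no assumption beyond the possibility that some subjects have low scores at both visits. The correction should be made because it is cheap and because the role should be fixed before the result is known.

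**What to change.** Reconcile the abstract, Study aims and Discussion by giving MoCA change one role. Either option is sound:

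1. **Secondary outcome.** Keep cognitive status in the aim. Report the Pre-Post change with a confidence interval, or the nonparametric equivalent that Statistical considerations implies for questionnaires. Delete the statement that an equal score is expected.
2. **Screen or check only.** Remove cognitive status from the secondary aim, so that it agrees with the Discussion's second objective.

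Under both options, delete the claim that Pre and Post MoCA will verify that cognition does not affect the other results. Examine that influence directly: enter the Pre MoCA score as a covariate in the regressions already planned, for change in OLSA, AQoL and HHIE-S. State that these analyses do not condition on Post MoCA or on MoCA change, since both are measured after fitting and may themselves be related to hearing-aid use.

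The cost is some rewording and one covariate, with no new data or visits. The sponsor gives up the claim that cognition has been ruled out as an influence and gains an estimate of how far the results vary with it.
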